## Abstract

**Background:**

Patients suffering from chronic, subjective tinnitus are on a quest to find a cure or any form of alleviation for their persistent complaint. Current recommended therapy forms provide psychotherapeutic interventions that are intended to train the patient how to deal with the tinnitus sound. Pharmaceutical managements are used to reduce secondary effects of the tinnitus sound such as sleep deprivation, emotional and concentration difficulties, but these treatments do not cure the tinnitus. Recent studies have shown that Tinnitus Retraining Therapy (TRT) significantly improves the quality of life for tinnitus patients. Furthermore, several studies have reported that cognitive behavioral therapy (CBT) relieves a substantial amount of distress by changing dysfunctional cognitions. However, when the tinnitus causes great interference with daily functioning, these treatment methods are not always sufficiently effective. Recent insights show that Eye Movement Desensitization Reprocessing (EMDR) is a highly effective therapy for medically unexplained symptoms such as chronic pain and phantom pain. In scientific research, tinnitus is compared to phantom limb pain. Starting from tinnitus as a phantom percept we therefore aim to demonstrate that the operating mechanisms of EMDR may also be an effective treatment method for patients with subjective tinnitus. The aim of this randomized controlled study with blind evaluator is to examine the effect of EMDR compared to CBT in chronic tinnitus patients.

To our knowledge, there are no other studies that evaluate both methods simultaneously.

**Methods/design:**

A total of 166 patients with subjective, chronic, non-pulsatile tinnitus will be randomized in two treatment groups: TRT + CBT versus TRT + EMDR. The experimental group will receive the bimodal therapy TRT/EMDR and the active control group will receive the bimodal therapy TRT/CBT. Evaluations will take place at baseline before therapy, at the end of the treatment and 3 months after therapy. The score on the Tinnitus Functional Index (TFI) will be used as the primary outcome measurement. Secondary outcome measurements are the Visual Analogue Scale of Loudness (VAS), Tinnitus Questionnaire (TQ), Hospital Anxiety and Depression Scale (HADS), Hyperacusis Questionnaire (HQ), psychoacoustic measurements and event-related potentials (ERP).

**Discussion:**

The objective is to evaluate whether the bimodal therapy TRT and EMDR can provide faster and/or more relief from the annoyance experienced in chronic tinnitus patients’ daily lives compared to the bimodal therapy TRT and CBT.

So far there has been no prospective, randomized controlled, clinical trial with blind evaluator that compares CBT and EMDR as a treatment for tinnitus.

**Trial registration:**

ClinicalTrials.gov, ID: NCT03114878. April 14, 2017.

**Electronic supplementary material:**

The online version of this article (10.1186/s13063-018-3121-6) contains supplementary material, which is available to authorized users.

## Background

Tinnitus is defined as the perception of sound without the presence of an external auditory input and, therefore, it is also referred to as a phantom percept [1]. Usually tinnitus is transient but 8 to 20% of the population suffers from chronic tinnitus. About 1–3% of this population experiences so much distress that they seek medical help [2]. Tinnitus sounds reported by patients are squeaking, buzzing or hissing sounds which can lead to a critical degree of psychological discomfort and can have a serious impact on one’s quality of life. There is a high co-morbidity found in patients suffering from more severe forms of tinnitus, such as depression, insomnia and anxiety [3]. The diagnosis and treatment, therefore, require great expertise to detect the existing etiology and co-morbidities. For the treatment of complex tinnitus cases, a multidisciplinary approach by ENT physicians, specialized audiologists and psychologists is required [4, 5]. Currently there is no pharmaco- or psychotherapeutic treatment that can alleviate chronic, subjective tinnitus. Effective forms of therapy such as Tinnitus Retraining Therapy (TRT) and cognitive behavioral therapy (CBT) are intended to teach patients how to deal with the tinnitus sound either through sound enrichment and psycho-education or through the alteration of cognitions. The clinical management for tinnitus over recent years consists of audiologic interventions and CBT [3, 6]. A stepped-care approach is recommended by guidelines that start with education as first step and end with specialized multidisciplinary CBT as the last step [7]. For a proportion of patients with tinnitus symptoms these treatment forms lead to a significant reduction of distress. When the tinnitus, however, causes a great interference with daily functioning, these treatment methods may not be sufficiently effective [7]. Recent research has shown that EMDR could be an effective therapy for medically unexplained symptoms such as chronic pain and phantom pain [8–12]. Francine Shapiro stated in 2001 that phantom pain can be perceived as a manifestation of the stored somatic memory [13]. The experiencing of pain while the limb is absent is an example of dysfunctional memory storage. Through EMDR treatment these somatic memory and pain sensations can be targeted and restored. Therefore, we hypothesize that EMDR may also be an effective treatment method for patients with subjective tinnitus. Tinnitus is known as phantom sound and previous research has shown overlapping brain networks between tinnitus and phantom pain [1]. Multiple dynamic brain networks such as the perception network, salience network, distress and memory network play a major role in eliciting and maintaining this phantom perception [1, 14, 15]. Previous research has shown that changes (i.e., neural plasticity) in the auditory system elicited by a sound trauma could cause tinnitus. This neural plasticity is a reaction of the nervous system when there is a reorganization and hyperactivity in the auditory cortex causing a tinnitus sensation [16, 17]. Magnetoencephalography (MEG) and electroencephalography (qEEG) earlier showed that different neural networks are at the basis of tinnitus loudness and tinnitus-related distress. Certain types of tinnitus are related to the reorganization and hyperactivity of the auditory central nervous system [18, 19]. Changes in neural activity were also observed in non-auditory brain areas [14]. The stress and emotional reactions associated with tinnitus probably find their neuronal correlate in networks at the level of the amygdala, the hippocampus and anterior cingulate cortex, the parahippocampus and the insula. Research shows that memory mechanisms play an important role in the persistence of the awareness of the phantom percept. Therefore, these mechanisms are inextricably linked to the reinforcement of the associated distress [1]. In these regions neuronal changes occur. We know that tinnitus is a phenomenon in which networks of auditory and non-auditory brain areas influence each other [1, 15, 20–22]. Hence, tinnitus viewed from the perspective of a trauma, more specifically in the auditory and limbic regions, leads to the need for effective information processing. The development of new neural networks could be generated through EMDR: bilateral stimulation promotes the plasticity of the brain causing neural networks to be adjusted. Recent studies demonstrate increase in limbic processing along with decreased frontal activation as a consequence of bilateral stimulation. These patterns of neural activity could facilitate the integration and reintegration of information [23, 24].

The use of bilateral stimuli to treat tinnitus is an innovative treatment method. In the literature, only limited data can be found in a few case studies where EMDR treatment is performed on tinnitus patients [25, 26]. These scarce data, however, provide insufficient insights concerning the EMDR treatment method and the mechanisms. Therefore, a randomized controlled study trial is necessary to examine the effectiveness of EMDR in persons suffering from tinnitus.

### Study objectives

The present study is a prospective, randomized controlled, clinical trial with blind evaluator in order to assess whether EMDR adds value to the treatment in chronic tinnitus patients. The general purpose of the current study is to examine a bimodal therapy for chronic, subjective tinnitus consisting of the combination of the TRT and EMDR. The goal of this treatment is reducing the subjective discomfort of tinnitus and thereby improving the quality of life of the patient.

## Methods/design

There will be three test moments during the trial: before the start of therapy (T0), after the treatment sessions (T1) and 3 months after the last therapy session (T2). The primary and secondary outcome measurements will be assessed at every test moment. The difference between bimodal therapy 1 (TRT + CBT) and bimodal therapy 2 (TRT + EMDR) will be assessed. The experimental intervention, namely TRT + EMDR, will be compared to the active control group, namely TRT + CBT, as shown in the Consolidated Standards of Reporting Trials (CONSORT) flow diagram in Fig. 1. The Standard Protocol Items: Recommendations for Interventional Trials (SPIRIT) Checklist was utilized as guideline for this study (Additional file 1).

**Fig. 1 Fig1:**
[figure not shown]
Consolidated Standards of Reporting Trials (CONSORT) study flow diagram. *TRT* Tinnitus Retraining Therapy, *CBT* Cognitive Behavioural Therapy, *EMDR* Eye Movement Desensitization Reprocessing

### Study population

Patients will be referred by the Ear, Nose and Throat (ENT) Department of the Antwerp University Hospital and will be randomized into group 1 (TRT + CBT) or group 2 (TRT + EMDR). The allocation sequence will be determined by the date the patients are referred to the study.

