### Study protocol

A number of 166 patients with subjective, chronic, non-pulsatile tinnitus will be randomized in two treatment groups: TRT + CBT versus TRT + EMDR. Licensed therapists will provide all treatments.

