### Primary outcome measurement

#### Tinnitus Functional Index (TFI)

The TFI is a self-reported questionnaire, consisting of 25 questions, which assesses the impact of tinnitus on patients’ daily lives [35, 36]. The patient answers each question on a Likert scale ranging from 0 to 10. Questions 1 and 3 are expressed in percentages, and the Likert scale ranges from 0 to 100%. The total score is calculated with the mean of all questions. The answers are converted and the total score is expressed as a number between 0 and 100. In addition to the total score, the score of eight subscales can be determined. The subscales are the following: intrusiveness, reduced sense of control, cognitive interference, sleep disturbance, auditory difficulties attributed to tinnitus, interference with relaxation, reduced quality of life and emotional distress.

A decrease in the score on the TFI in the TRT-CBT treatment group versus a decrease in the TFI score in the TRT- EMDR-treatment group is the primary focus of attention in this study.

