### Sample size calculation

A sample size calculation was carried out to determine the sample size required to obtain a power of 80% with α = 0.05 in a two-sided, two-sample *t* test. Assuming an average difference of 0.7 SD between both treatment groups – simplifying the calculation by considering the change in outcome between the first and the last point – a power of 80% is reached with minimal sample size of 65 patients per treatment group. To cover possible drop out, 166 patients will be randomized between therapy group TRT + CBT and therapy group TRT + EMDR. The CONSORT guidelines will be followed and the enrollment data will be transferred into the flow diagram.

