### Dissemination protocol

According to the Standard Protocol Items: Recommendations for Interventional Trials (SPIRIT) guidelines, the authors declare that data that break the blind will not be presented prior to release of mainline results. Breaking of the blind will occur at the end of the study. A clinical article will be written on the primary and secondary outcomes of the study and will be disseminated regardless of the magnitude or direction of effect. The present trial is not industry initiated; therefore, there is no publication restriction imposed by sponsors. In addition, a full study report with an anonymized participant-level dataset and statistical code for generating the results will be made publicly available no later than 3 years after termination of the study for sharing purposes.

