### Trial status

To date, patient recruiting is in the final phase. More than 100 patients have been randomized and have ended treatment or are being treated. The end date of study will be June 2019.

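### As written, the allocation sequence follows the date of referral, a systematic rule that contradicts the randomized label, and no concealment is described

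*Protocol article*

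**What the plan says.** The protocol article gives one allocation rule, in the Study population section: "The allocation sequence will be determined by the date the patients are referred to the study". The sentence before it reads "Patients will be referred by the Ear, Nose and Throat (ENT) Department of the Antwerp University Hospital and will be randomized into group 1", with the TRT + EMDR group named as the alternative. The Study objectives section states "The present study is a prospective, randomized controlled, clinical trial with blind evaluator". The Study protocol section states "A number of 166 patients with subjective, chronic, non-pulsatile tinnitus will be randomized in two treatment groups: TRT + CBT versus TRT + EMDR". The abstract's Methods/design paragraph and the Sample size calculation section also describe the allocation as randomized. The Trial status section reports "More than 100 patients have been randomized and have ended treatment or are being treated".

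On masking, the article claims a blind evaluator, and the Dissemination protocol section adds "Breaking of the blind will occur at the end of the study". Both concern what happens after entry. Nothing in the article describes keeping the next assignment hidden from those who refer or enrol patients.

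**The concern.** A sequence fixed by a calendar date contains no chance element. It is a systematic method, so the rule and the randomized label cannot both be literally true. The problem lies in what the article states. It does not arise from detail left to a fuller document: the article names what determines the sequence, and what it names is not random.

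The date also arises with the party that sends the patients, the ENT department of the same hospital. If that department knows how dates map to arms, it can tell which arm a patient would join. It could then delay, bring forward or withhold a referral for a patient thought to suit one therapy better.

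The later safeguards do not reach this. A blind evaluator protects outcome assessment and does not govern who enters which arm. The primary outcome is in any case the patient's own rating: "The TFI is a self-reported questionnaire, consisting of 25 questions". The mixed model in Statistical methods lists intervention group and test moment as its fixed effects. Adding measured covariates would not remove selection on unmeasured prognosis. At stake is the causal reading of the EMDR versus CBT comparison.

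**Working it through.** **1. The statements side by side.** Abstract (Methods/design), Study objectives, Study population (first sentence), Study protocol, Sample size calculation and Trial status: allocation is randomized. Study population (second sentence): the sequence is determined by referral date. No other section gives a sequence method that would override the second sentence.

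**2. Foreseeability.** Under a fixed date rule that the referrer knows, every next assignment can be foreseen (100%). For comparison, the share guessed correctly is 50% under simple 1:1 randomisation, and about 71% under permuted blocks of 4 when past assignments are visible (simulated). The 100% is an upper bound, since the article gives neither the mapping from date to arm nor who knows it.

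**3. The plan's own sample size, to fix the unit.** The plan requires "a power of 80% with α = 0.05 in a two-sided, two-sample *t* test", with a difference of 0.7 SD and 65 patients per group.
- Formula: n per group = 2 × (1.960 + 0.842)² × σ² / 0.7², where (1.960 + 0.842)² ≈ 7.85.
- With σ = 1 SD: 2 × 7.85 / 0.49 = 32.04, so 33. This does not match 65.
- With σ = √2 SD: 2 × 7.85 × 2 / 0.49 = 64.1, so 65. This matches.

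The figure of 65 is therefore reproduced only if the SD of change is √2 times the SD in which 0.7 is expressed. The article does not state this, so both units are carried forward.

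**4. Illustrative effect on type I error.** Let b be the prognostic difference in change between arms produced by steering. The values of b are assumptions; the article gives none. With 65 per arm, SE = σ × √(2/65), the shift is z = b / SE, and the true two-sided error is P(Z > 1.96 − z) + P(Z < −1.96 − z).

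| σ | SE | b | z | Type I error |
|---|---|---|---|---|
| 1 SD | 0.175 | 0.1 SD | 0.57 | 8.8% |
| 1 SD | 0.175 | 0.2 SD | 1.14 | 20.7% |
| √2 SD | 0.248 | 0.1 SD | 0.40 | 6.9% |
| √2 SD | 0.248 | 0.2 SD | 0.81 | 12.7% |

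**5. What a split by allocation period could show.** At most about 166 − 100 = 66 patients remain. Taking 50 per arm already allocated and 33 per arm still to come, with σ = 1 SD and no dropout, the SE of the difference between the two periods' treatment effects is √(2/50 + 2/33) = √(0.0400 + 0.0606) = 0.317 SD. The 95% interval then extends about 1.96 × 0.317 = 0.62 SD either side, far wider than the biases in step 4.

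**The case against.** The strongest reply is that the two sentences in Study population can be reconciled: patients are randomized, and the referral date only fixes the order in which they take the next place on a random list. The article gives no rule tying dates to arms, such as odd and even days or alternation. This stands as a possibility, and it rules out a flat statement that the trial is not randomised. It does not rescue the sentence, which says that the date determines the sequence itself, not a patient's place in it.

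A reader might also infer that the trial claims concealed allocation and fails to deliver it. The documents do not support that. They claim randomisation and a blind evaluator and never claim concealment; an article may leave list, block and concealment details to the full protocol. Nor do they show that the ENT department knew a rule or acted on one, so foreseeability is conditional.

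It is fair, too, that the sample size reasoning looks at change from first to last point and that the mixed model includes T0. A mere difference in baseline TFI level is therefore at least partly handled. What carries through is selection on prognosis for change, which is how b is defined above. Adding T0 TFI as a covariate is no simple repair: T0 is already a level of test moment in the outcome, so it would appear on both sides of the model unless removed from the outcome vector.

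Finally, the error rates depend on assumed biases and on the SD unit. That is correct, and they are given only as illustrations.

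**Conclusion.** The allocation sentence is wrong as written and must be replaced. Read literally, it sets a systematic rule that contradicts the randomized label used throughout the article. This conclusion rests on the text alone and needs no figure.

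Whether the trial was in fact quasi-randomised depends on the rule actually used, which the article does not settle. Whether selection occurred, and how much, is unknown. If steering produced a difference in prognosis for change of 0.1 to 0.2 SD, the two-sided type I error would be about 9% to 21% with the SD of the analysed outcome as the unit. It would be about 7% to 13% if the SD of change is √2 times that unit, the value that reproduces the planned 65 per group. The plan's sample size, power and alpha figures are not altered by this point.

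**What to change.** - **Remaining patients:** replace the sentence. Assign the arm from a computer-generated random list with varying block sizes, held by someone outside referral and therapy, and revealed only after consent and T0 testing.
- **The more than 100 patients already allocated:** report the rule actually used. If it was date-based, describe that part of the trial as quasi-randomised, name it as a limitation, and report a sensitivity analysis by allocation period, stating its low precision (step 5).
- **If referral date only set the order** in which patients took the next place on a concealed random list, rewrite the sentence to say exactly that, and say how the list was generated and held. The quasi-randomised label then does not apply.

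The cost is a short amendment, a random list that is free to produce, and open disclosure of how earlier patients were allocated. Recruitment is in its final phase, so the new list can protect only the minority still to enter. Disclosure is therefore the more important part of the change.

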### Inclusion and exclusion criteria

The appropriate ENT and audiological examinations will be performed in order to assess whether a patient meets the inclusion criteria. During the study, the patient has the right to cease the study at any time. The occurrence of severe adverse events can also lead to discontinuation of the study.

The inclusion criteria are as follows:Tinnitus type: chronic, subjective, non-pulsatile tinnitusDuration of tinnitus = more than 3 monthsMinimum age of the patient is 18 years old – maximum age is 75 years oldTinnitus Functional Index (TFI) score ≥ 25 to < 90Stable use of medication during therapy

A patient is excluded from the study for the following reasons:HADS – score: anxiety and depression subscores > 15HQ – score > 40Objective, pulsatile tinnitusActive middle-ear pathologyNeurological and psychiatric co-morbidity for which acute psychotherapy is ongoingPsychosis, schizophrenia, epilepsyPregnancy

### Study protocol

A number of 166 patients with subjective, chronic, non-pulsatile tinnitus will be randomized in two treatment groups: TRT + CBT versus TRT + EMDR. Licensed therapists will provide all treatments.

#### Tinnitus Retraining Therapy

TRT is a therapy originally developed by [name] and [name] [27]. During the counseling, the patient is educated about the working mechanism of tinnitus and how to deal with the emotional and physical responses. The main goal is to habituate to the sound of the ringing in the ears. Every patient will receive five 60-min sessions of TRT. The TRT will consist of counseling, sound enrichment and adjustment of a noise masker. A licensed tinnitus therapist will perform the TRT sessions using the patient counseling guideline of Henry et al. [28].

#### Cognitive behavioral therapy

CBT is the combination of behavioral therapy with interventions that have been developed from cognitive psychology. The founders of CBT are Aaron Beck and Albert Ellis [29]. The core idea is the assumption that so-called negative cognitions are responsible for dysfunctional behavior. The techniques used in CBT focus on changing the content of these irrational cognitions. The way tinnitus influences our daily functioning is largely dependent on the meaning we give to this sound and the thoughts we have associated with tinnitus determine which emotional reactions are triggered. CBT helps the patient to change the thoughts associated with tinnitus and as a consequence, alter the emotional response. Mindfulness and a number of relaxation techniques were also developed within CBT. The interventions are based on a 4-year postgraduate training in CBT and a tinnitus master class by [name] in 2013. [name] BSc, MSc, PhD focuses on researching and providing specialist therapy for patients experiencing tinnitus [30].

Following treatment outline will be the guideline for the CBT sessions Table 1.

**Table 1 Tab1:** Intervention based on the cognitive behavioral therapy (CBT) treatment outline

Phase number	Treatment outline
Phase 1	Educating the patient about the auditory system (brief, only if necessary after TRT sessions)
Phase 2	Introduction of CBT and assess the motivation and commitment towards the therapy
Phase 3	Help identify thoughts, emotions and behavior in response to sound
Phase 4	Help identify negative automatic thoughts and core belief
Phase 5	Education about common errors of judgment and distortions in thoughts
Phase 6	Challenging unhelpful thoughts and creating counterstatements
Phase 7	Empirical demonstration: experiencing the consequence of helpful thoughts
Phase 8	Behavioral desensitization and graded exposure

Note: CBT treatment outline by [name] based on handouts and personal communication from the Tinnitus and Hyperacusis Master Class in March 2013 at Birkbeck College, London

Every patient who is randomized into the TRT + CBT – group will receive five 60-min sessions of CBT performed by a licensed clinical psychologist and psychotherapist specialized in CBT.

